### Measures

#### Outcome measures

An overview of outcome measures is presented in Table 2.

**Table 2 Tab2:** Outcome measures

Domain	Specific measurement	Metric	Method of aggregation	Time point		
				Baseline	Training	Post-intervention
Interpretation bias	Interpretation speed of secure and insecure scenario resolutions	Difference between secure and insecure resolutions	Mean reaction time to secure and insecure probes		x	
	Secure interpretation bias	Change from pre-intervention to post-intervention recognition task	Mean rating of secure interpretations	x		x
	Insecure interpretation bias	Change from pre-intervention to post-intervention recognition task	Mean rating of insecure interpretations	x		x
Trust	PIML Trust subscale	Change from pre-intervention to post-intervention	Mean rating of trust items	x		x
Child’s attachment-related behavior	Observation of the quality of the approach of child towards mother during a puzzle task with the MCAM scoring scales	Change from pre-intervention to post-intervention	Frequency of child behaviors	x		x
Mother-child interactional coherence	Observation of positive parent behavior and positive child behavior (with the MCAM scales) during a puzzle task	Change from pre-intervention to post-intervention	Jaccard Index indicating the occurrence of parent behavior at time point t − 1 and child behavior at time point t and vice versa (i.e., indicating the occurrence of child behavior at time point t − 1 and parent behavior at time point t)	x		x

*PIML* People In My Life; *MCAM* Middle Childhood Attachment Micro-observation system

##### Interpretation bias

We assess interpretation bias with two different measures: interpretation speed of secure and insecure scenarios, and spontaneous interpretation of new attachment-related information.

##### Interpretation speed of secure and insecure resolutions

We assess interpretation speed of secure and insecure resolutions of ambiguous maternal behavior during training. As aforementioned, in both conditions, each block contains two probe scenarios: one secure and one insecure (12 probes in total). The format of the probe scenarios is the same as that of the training scenarios. For the secure probes, the resolution of the scenario is always secure (i.e., mother provides support). For the insecure probes, the resolution of the scenario is always insecure (i.e., mother does not provide support). We randomized presentation of the probe and training trials within each block, with the final order kept identical for all participants. We test differences between intervention groups in interpretation speed of secure versus insecure scenarios using mean reaction times to secure and insecure resolving word fragments separately. Faster mean reaction times to secure probes and slower mean reaction times to insecure probes indicate a more secure interpretation bias.

##### Change in secure interpretation and insecure interpretation of ambiguous maternal behavior

Before and after intervention we measure children’s spontaneous interpretation of ambiguous maternal behavior by means of a recognition task [23, 56]. During this task children read seven 3-line scenarios and, as in the training, a word is missing in the last line. The next screen shows the missing word as a word fragment and children have to press the space button as quickly as possible when they can complete this fragment. Subsequently, they press the missing letter on the keyboard. After resolving the word fragment, however, it remains ambiguous whether or not mother provided support. To make sure that children actively read the scenarios, they have to answer a yes/no comprehension question after each scenario followed by feedback on their answer. Once children have read all seven scenarios, we measure their interpretation bias. Specifically, for each scenario, two events are described: one secure event (i.e., describing supportive maternal behavior) and one insecure event (i.e., describing unsupportive maternal behavior). For each event, children have to indicate to what extent they think the described event occurred in the scenario on a 4-point Likert scale ranging from 1 (completely untrue) to 4 (completely true). However, none of the events actually occurred in the scenarios. Therefore, the scores measure children’s spontaneous interpretation of ambiguous maternal behavior. Change in secure and insecure interpretations is examined separately. An increase in scores for the secure events means a more secure interpretation bias. Likewise, an increased score for the insecure events indicates a more insecure interpretation bias.

##### Change in trust

We measure trust in mother with the Trust subscale of the People In My Life Questionnaire (PIML) [57]. This subscale contains 10 items concerning experiences with mother as a trustworthy source for support (e.g., “I can count on my mother to help me when I have a problem”). Children have to indicate how true the item is for them on a Likert scale ranging from 1 (almost never true) to 4 (almost always true). We administer the subscale before intervention to determine baseline trust in maternal support. Shortly after intervention we readministered the scale to allow assessment of change in trust. The PIML is a valid self-reported measure for middle childhood [14] and has been used in previous research to assess change in trust in maternal support [23].

##### Change in observed behavior during a distressing task

We assess changes in behavior of children towards mother and in mother-child interactional behavior by means of videotaped observation of mother-child interaction during a distressing puzzle task. Researchers have used this puzzle task, taken from Rush Hour Traffic Jam Puzzle®, before to observe attachment behavior in a distressing situation in middle childhood [58, 59]. In this task, a red car’s path out of a traffic jam is blocked by other cars and trucks. The child has to move the other cars to free the path for the red car. After the experimenter explains the rules, children first solve a simple practice puzzle. Subsequently the child receives an unsolvable puzzle with the instruction that their mother is allowed to help. The experimenter tells children that the puzzle is not very difficult, that most children their age can solve the puzzle in less than 5 min, and that, therefore, they are also given 5 min to solve the puzzle. A laptop screen shows a stopwatch so that the child can see how much time is left. The combination of trying to solve an unsolvable puzzle under time pressure and social comparison with peers effectively induced stress in previous research [59]. After starting the stopwatch the experimenter leaves the room. Three minutes later the experimenter returns and aborts the attempt to solve the puzzle with the excuse that, on account of the timing of the procedure, they have to proceed with the rest of the tasks. The experimenter then says that the mother-child dyad will be given another chance to solve the puzzle when there is time left at the end of the procedure. The attempt to solve the puzzle is terminated after 3 min instead of 5 min so children do not specifically fail on the first attempt, but are merely given too little time to solve it. This with the aim to increase comparability between the pre-intervention and post-intervention puzzle tasks.

We administer the same puzzle task post-intervention. Participants receive the same instructions as pre-intervention, after which the experimenter starts the stopwatch and leaves the room. Three minutes later the experimenter enters again and stops the attempt to solve the puzzle by asking the mother-child dyad whether they already succeeded in solving the puzzle. As a manipulation check the experimenter asks – first the child, then the mother – if they know how it is possible that they were not able to solve the puzzle.

We videotape the pre-intervention and post-intervention puzzle task and code mother and child’s verbal and nonverbal behavior by means of the Middle Childhood Attachment Micro-observation system (MCAM) [42]. The MCAM was based on the emotional attachment scales (EAS middle childhood version) [60] and the Strange Situation Procedure (SSP) [3], and researchers have used it before to register mother-child interactions during a similar puzzle task [42, 43]. The MCAM distinguishes six global child behavior categories: responsiveness; involving the parent (i.e., proximity-seeking); clinging and controlling behavior; closeness and interaction avoidant behavior; closeness and interaction opposing behavior; and puzzle behavior (together versus alone). In the present study, we use partial-interval recording to code the occurrence of behaviors in all MCAM categories every 2 s [61]. We assess frequency of these behaviors for the pre-intervention and post-intervention puzzle task to evaluate change in trust-related behavior towards mother due to the interventions.

To assess change in mother-child interactional coherence, we also code mother’s behavior using partial-interval recording. The MCAM distinguishes five global parent behavior categories: parental sensitivity; parental structuring; noncontingent response; parental hostility; and puzzle behavior (together versus alone). Using the Jaccard Index [62], we assess the extent to which positive parent behavior (as coded in the categories parental structuring and parental sensitivity) at time point t − 1 is predictive of positive child behavior (as coded in the categories responsiveness and involving the parent) at time point t. Additionally, we explore whether positive child behavior at time point t − 1 is predictive of positive parent behavior at time point t. Coders are blind to the intervention condition (both training and nasal spray condition) that the mother-child dyads are in.

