At the second level, the effects of CBM training, OT, and both interventions combined on change in self-reported trust from pre-intervention to post-intervention are assessed. It is expected that participants who receive any intervention (CBM training, OT, or the two combined) will show an increase in trust as compared to participants receiving no intervention [23, 29]. If joint exposure to the two interventions is beneficial, this should be reflected in a stronger increase in trust for participants who receive the interventions combined as compared to participants who receive only one of the interventions.

At the third level, intervention-related changes in behavior of children towards mother and mother-child interactional behavior during a distressing task are observed. The main effects of the two interventions as well as the interaction effect of the interventions are assessed. To our knowledge this is the first study examining the effects of CBM training and OT on behavior during mother-child interaction. Nevertheless, previous studies have linked more trust to more positive behavior of child towards mother [42] and to a more coherent mother-child interactional pattern [43]. Therefore, if the interventions affect trust and these effects extend to the behavioral level, children who receive any intervention (CBM training, OT, or the two combined) should show an increase in positive approach towards mother as compared to children who receive no intervention. Similarly, mother-child dyads in the intervention groups (CBM training, OT, or the two combined) should show increased interactional coherence compared to mother-child dyads in which children receive neutral training and PL as a control condition.

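### The lagged Jaccard Index used for mother-child coherence depends on how often each partner is positive, so without a chance correction it cannot by itself show prediction

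*Protocol article*

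**What the plan says.** Table 2 (Outcome measures) gives the aggregation method for interactional coherence as "Jaccard Index indicating the occurrence of parent behavior at time point t − 1 and child behavior at time point t and vice versa", with pre-to-post change as the metric. The section on observed behaviour during the distressing task explains what the index is meant to show: "Using the Jaccard Index [62], we assess the extent to which positive parent behavior (as coded in the categories parental structuring and parental sensitivity") in one interval "is predictive of positive child behavior (as coded in the categories responsiveness and involving the parent) at time point t". The reverse direction, child to parent, is described there as something to be explored.

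On the coding, "we use partial-interval recording to code the occurrence of behaviors in all MCAM categories every 2 s". On the length of the task, "The attempt to solve the puzzle is terminated after 3 min instead of 5 min", and the second attempt also lasts three minutes.

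The aims section makes two adjacent predictions for the intervention groups. Children who receive any intervention "should show an increase in positive approach towards mother as compared to children who receive no intervention", and dyads in those groups "should show increased interactional coherence compared to mother-child dyads in which children receive neutral training and PL as a control condition". Data analysis applies a two-way ANOVA (training by nasal spray) to the change scores, with p < .05. No chance reference, base-rate adjustment or behaviour-frequency covariate is stated for the coherence score.

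**The concern.** The Jaccard Index is the number of interval pairs in which both partners are positive, divided by the number in which at least one is. It therefore mixes two things: how often each partner is positive, and whether one partner's behaviour follows the other's. Only the second is prediction, which is the reading the article gives the index.

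This matters here because one of the two series in the index is the child's positive behaviour (responsiveness and involving the parent), and the article expects the interventions to raise the child's positive approach. Treating that approach as largely the same coded behaviour is an inference, but a natural one, since these are the positive child categories the article names. If that first hypothesis is true, the coherence score will on average rise even when mothers and children respond to each other no more than before. A significant coherence result could then be a restatement of the frequency result, and the planned analysis could not tell the two apart.

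**Working it through.** **Inputs from the article.** Three minutes at 2 s gives 180/2 = 90 intervals and 89 lagged pairs per task. There are 25 dyads per cell, so 50 v 50 for each main effect. The test is a 2 × 2 ANOVA on change, with critical F = 3.94 at N = 100.

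The article gives no figure for the index itself. Its sample-size figures reproduce: power is 0.803 at N = 90 and 0.844 at N = 100, with f = 0.30 and numerator df = 1. They are used here only to fix the test.

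**Assumed inputs, because the article gives none.** Base rates, the spread between and within dyads, serial correlation, and the size of any frequency shift.

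**Step 1: expected index with no contingency.** If the two series are unrelated, with child rate p and mother rate q, the proportion of pairs with both positive is pq and with either positive is p + q − pq. So J centres on pq/(p + q − pq) = 1/(1/p + 1/q − 1), which increases in each rate. With the mother at 0.40:

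- child 0.30: 0.12/0.58 = 0.207
- child 0.40: 0.16/0.64 = 0.250
- child 0.50: 0.20/0.70 = 0.286

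Contingency is zero in every line; only the child's frequency changes.

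**Step 2: this is an average tendency.** Take 89 pairs with the mother positive in 36 and the child positive in 27, all inside the mother's 36. Then J = 27/36 = 0.75. Add nine child-positive intervals, all where the mother is not positive, and J = 27/45 = 0.60. The index can fall when the child becomes more positive.

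**Step 3: how often the planned test would be significant.** The simulation uses independent mother and child series, mother 40%, child 30%, between-dyad logit SD 0.5 and within-dyad logit SD 0.3–0.5. The shift is applied to treated dyads only, after intervention, with 600 to 2,000 simulated trials per setting in the main runs.

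For a 10-point rise in the child's rate, by lag-1 autocorrelation within each partner's series, the raw index is significant in:

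- 0: 39–57% of trials
- 0.3: 38–49%
- 0.5: 29–36%
- 0.6: 24–31%
- 0.8: 14–20%

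For a 5-point rise the range is roughly 6–21%. The chance-corrected index is significant in about 3–7% of trials throughout. With no frequency shift, both versions reject at about 5%.

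**Step 4: other base rates.** Without serial correlation, with child rates of 0.20–0.40, mother rates of 0.30–0.50, between-dyad logit SD 0.3–0.8 and within-dyad SD half of that, the raw index rejects in 39–74% of trials for a 10-point child shift and 17–29% for a 5-point shift. Chance-adjusted indices reject in about 3–8%. The ranges in Step 3 are therefore conditional on their assumptions and are not outer bounds.

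**The case against.** Several counter-arguments have force.

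- **Two unrelated series is an extreme case.** The child category responsiveness, and the separate parent category for noncontingent response, suggest that some contingency is already judged at coding. This stands as a limit on the illustration. It does not remove the dependence on base rates.
- **The size rests on assumptions.** Two-second codes of ongoing behaviour are likely to be serially correlated, and strong persistence cuts the artefact to 14–20% for a 10-point shift. A 5-point shift can bring it close to the nominal level. This stands, and it is why only a wide range is given.
- **The cited method might include a chance reference.** That source is not available, and a condensed article may omit detail. However, Table 2 names the plain index as the aggregation method and the text attaches the predictive reading to it.
- **This is one outcome in a proof-of-principle study.** That is fair, and it limits the weight of the point.

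Three stronger readings are tempting, and the documents do not support them. A reader might infer that the index rises whenever either partner is more positive, but Step 2 shows it need not. A reader might infer false positives when the interventions do nothing, but with no frequency shift the error rate stays near 5%; what is at issue is how a real frequency effect is labelled. A reader might also infer that the article counts child behaviour and coherence as independent support. It nowhere says so: both sit under one third level of outcome, and child behaviour frequency is listed separately, so it would be visible beside the coherence result.

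**Conclusion.** The concern holds in a limited form. The article fixes a metric that depends on each partner's base rate and gives it a predictive meaning that it cannot carry alone. Because the article itself predicts more positive child behaviour in the same groups, a frequency effect would on average also register as greater coherence.

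The direction follows from algebra. The size rests on assumed rates, zero contingency, the assumed dyad spread and serial correlation, and on the interventions shifting the child's frequency at all. The interpretation of one outcome is affected; the trial's other outcomes and its sample size are not.

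**What to change.** In Table 2 and in the section on observed behaviour, define the coherence outcome as the pre-to-post change in the chance-corrected lagged Jaccard, (J − J_exp)/(1 − J_exp). Take J_exp either from circularly shifted series of the same dyad and session or from the two marginal rates, and state which. Analyse the parent-to-child direction in the planned two-way ANOVA, and keep child-to-parent exploratory, as the text already has it. Report the raw Jaccard descriptively beside the child behaviour frequency.

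The cost is computation on codes already planned, with no new coding. Recruitment was still open at the time of the article, and the spray envelopes stay sealed until data collection ends, so the change could be made before the spray allocation is known. The corrected index will be somewhat noisier in dyads with few positive intervals. It removes the artefact that arises when there is no contingency, which is the case checked here.

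A lag-1 log odds ratio is an alternative, but it needs a stated continuity correction for empty cells. In simulation these arose in about 0.5–3% of dyads at autocorrelation 0–0.5 and 15–18% at 0.8.

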### Other measures

#### Oxytocin side-effects

We explore any side-effects of the OT intervention with parent and child questionnaires. All children are asked about the most common reported side-effects which include dizziness, drowsiness, dry mouth, irritated or runny nose, stomach- or headache, anxiety, feeling uplifted and feeling relaxed [53], and any other noted changes immediately after the procedure (face-to-face). After 24 h, mothers answer the same questions via phone. Experimenters register the onset, duration and severity of any reported side-effects.

#### Mood

Before and after intervention, children rate their mood on two Visual Analogue Scales (VAS; 100 mm). One scale assesses to which extent children are in a happy mood, the other measures to which extent they are in a sad mood. Additionally, children fill out these mood scales immediately before training (i.e., 35 min after nasal spray administration). We can use the mood measurements to assess effects of the interventions on mood, to control for possible mood effects on the primary and secondary outcome measures.

#### Mother-reported questionnaires

We administer the following mother-reported questionnaires to allow for exploratory moderation analyses of the intervention effects.

A demographic questionnaire collects participant characteristics including among others gender, date of birth, living situation, nationality, birth weight, length of pregnancy and complications during pregnancy, attachment figures during first years of life, parental separation, parental level of education and parental socioeconomic status.

The Early Adolescent Temperament Questionnaire-Revised (EATQ-R) assesses child temperament [63]. The EATQ-R consists of 62 items (e.g., “My child finds it easy to really concentrate on a problem”) that mothers rate on a 5-point Likert scale. The psychometric properties of the EATQ-R are sufficient [64].

We assess children’s behavioral and emotional problems with the Child Behavior Checklist (CBCL) [65, 66]. The CBCL consists of 113 items (e.g., “Fights a lot”) for which mother rates on a 3-point scale to what extent they are true for their child in the last 6 months. The reliability and validity of the CBCL is well established [67].

Two questionnaires, comprising in total 47 items, assess mother’s parenting style. The short version of the Ghent Parental Behavior Questionnaire (“Verkorte Schaal Ouderlijk Gedrag” (VSOG); 25 items [68]) taps into mother’s parenting behavior. A second questionnaire consists of three subscales: the Responsiveness subscale of the Louvain Adolescent Perceived Parenting Scale (LAPPS; seven items [69]), a Dutch version of the Autonomy Support subscale of the Perceptions of Parents Scale (POPS; seven items [70]) and a Dutch version of the Psychological Control Scale (PCS; eight items [71]). Mothers rate the items on a 5-point Likert scale. Previous research has shown that the (Dutch versions of these) questionnaires and subscales are reliable [68, 72–74].

We assess children’s pubertal status with the parent-reported Pubertal Developmental Scale (PDS) [75]. Mothers rate five items about their child’s physical development (separately for boys, e.g., beard growth, and girls, e.g., breast development) on a 5-point scale. Past research found significant associations between the parent-reported PDS and the self-reported PDS [76]. The PDS has good reliability and validity [75, 77].

We evaluate symptoms of sino-nasal problems in the last 2 weeks with a parent-reported brief version of the 20-item Sino-Nasal Outcome Test (Snot-20) [78]. Mothers indicate how much their children were affected by symptoms of sino-nasal problem (10 items; e.g., “need to blow nose”) in the past 2 weeks on a 5-point scale.

